### 3.6.2 Sociodemographic Questionnaire

This self-developed questionnaire will be used to collect participant's personal information, including age, gender, occupation, hand dominance, history of present injury including date of injury, mechanism of injury, medical/surgical

management and date of surgery, employment status, and compensation scheme. The Sociodemographic Questionnaire is shown as in Appendix B.

### 3.6.3 Disabilities of the Arm, Shoulder and Hand (DASH) Outcome Measure

The Disabilities of the Arm, Shoulder and Hand (DASH) Outcome Measure is an extensively researched evaluative and discriminative region-specific patient-rated outcome measure used by many clinicians and researchers in the field of hand therapy. This instrument was first developed by the American Academy of Orthopedic Surgeons, the Council of the Musculoskeletal Speciality Societies, and the Institute for Work and Health (IWH), Toronto (Ontario), and published in 1996 (Hudak et al. 1996; Klerk et al. 2018). The DASH was developed to be a measure of physical function and symptoms for any or multiple musculoskeletal conditions of the upper limb (Kennedy & Beaton 2017). The DASH has multiple language versions including the Malay (Al-Husunny et al. 2011) and Simplified Chinese (Chen et al. 2015). There is extensive research evidence of its psychometric properties (Klerk et al. 2018). The DASH is a 30-item questionnaire that evaluates symptoms and physical function (at the level of disability), with a five response option for each item. The total score of DASH is calculated using the provided formula with higher score indicates greater disability (MacDermid 2000).

DASH score formula:

$$\text{Total score} = \left( \left[ \frac{\text{sum of } n \text{ responses}}{n} \right] - 1 \right) \times 25$$

Evidence was provided of the validity, test-retest reliability, and responsiveness of the DASH. The DASH is useful across the whole upper extremity with its demonstrated validity and responsiveness in both proximal and distal disorders (Beaton et al. 2001). According to study by Beaton et al. (2001), the DASH outcome measure exceeded recommended standards for test-retest reliability for both individual-and group-level interpretation of the scores (Intraclass correlation coefficient, ICC=0.96). Convergent construct validity was shown by demonstrating moderate to high correlations with other markers of disability and symptoms (Pearson Product Moment Correlation Coefficient = 0.68–0.92 while Spearman correlations=0.69–0.92). Discriminative validity was confirmed by showing differences between the DASH scores of patients who were working

and those who were not (26.8 vs. 50.7,  $t=-7.51$ ,  $p<0.0001$ ) as well as patients who were functioning and the scores of those who were not (23.6 vs. 47.1,  $t=-5.81$ ,  $p<0.0001$ ). The DASH is responsive to the different types of change before and after treatment of the target conditions (Standardized Response Mean, SRM=0.74-0.80) and in those patients whose ability to function had improved (SRM=0.92-1.40). The Malay version of DASH has internal consistency, Cronbach's  $\alpha$  0.99 and test-retest reliability, ICC=0.94 (Al-Husunny et al. 2011). The DASH Outcome Measure that will be used (English, Malay, and Chinese versions) are attached as Appendices C, D and E.

#### 3.6.4 LAM Assessment on Stages of Employment Readiness (LASER) Questionnaire

The Lam Assessment on Stages of Employment Readiness (LASER) was developed to measure one's psychological readiness to return to work after an extended period of unemployment due to disability (Lam et al. 2010). LASER contains 14 items corresponding to Prochaska's stages of change model which describe behaviours in the pre-contemplation (6 statements), contemplation (4 statements) and action stages (4 statements). The workers are asked to rate each item on a five-point Likert Scale with "1" indicating strongly disagree to "5" indicating strongly agree. The scores are then added and allocated under different sub-scores representing the corresponding stages as forming a continuous measure. The highest sub-score will represent a subject's tendency towards the corresponding stage. Subjects at the pre-contemplation (PC) stage do not see unemployment as a problem, and are often not interested in working, or believe that they cannot work. Subjects at the contemplation (C) stage begin to consider the pros- and cons- of working, but they have not yet participated in any related action such as job searching. Subjects at the action (A) stage have decided to work by engaging in job seeking behaviours and removing many of the barriers related to returning to work (Chan et al. 2006). The correlations between the factors were  $-0.50$  (between PC and C),  $-0.56$  (between PC and A), and  $0.74$  (between C and A), and the correlations between the three pairs of error terms were 0.34, 0.33, and 0.27. The Cronbach's alphas (a measure of internal consistency) for the Pre-contemplation and Contemplation scales are 0.77 and the Action scale is 0.82 (Lam et al. 2010). The LASER Questionnaire has been

translated to both Chinese and Malay languages. Both translated versions of LASER Questionnaires have shown good test retest reliability. The intraclass correlation coefficient (ICC) for the Chinese version ranged from 0.55 to 0.79 (Chan et al. 2006) while the ICC for the Malay version ranged between 0.707 and 0.917 (Chandran & Jamaludin 2009). The LASER Questionnaire (English, Malay, and Chinese versions) that will be used are attached as Appendices F, G, and H.

### 3.6.5 Visual Analogue Scale (VAS)

The Visual Analogue Scale (VAS) is a reliable and valid instrument commonly used for measurement of pain intensity in rehabilitation (Crossley et al. 2004). It is a single-item instrument that measures the whole construct at once. It consists of a 100mm horizontal line anchored with two opposite labels, i.e. no pain and severe pain; patients mark a score on the scale using a vertical line. Because VAS is easy to use, it is applicable to a variety of practice and research settings (Boonstra et al. 2008). The VAS that will be used are attached as Appendix I.

### 3.6.6 Goniometer

Range of motion measurement will be done by using the goniometer. Active and passive ROM of the wrist and fingers of the fractured wrist will be assessed (Adams et al. 2003; Bland et al. 2008; Goldhahn et al. 2014; Waljee et al. 2016). Active ROM of the wrist joint, including wrist flexion, wrist extension, wrist radial deviation, wrist ulnar deviation will be assessed first, followed by AROM of the forearm rotation i.e. supination and pronation. Following AROM, passive ROM will be moved to end range in order to assess end feel. Passive ROM begins with the wrist flexion, wrist extension, wrist radial deviation, and wrist ulnar deviation. Following wrist motion, passive forearm rotation, i.e., supination and pronation will be tested to assess movement ability of proximal and distal radioulnar joints (Porretto-Loehrke et al. 2016). Active and passive ROM of the fingers' metacarpophalangeal joint (MCPJ), proximal interphalangeal joint (PIPJ), and distal interphalangeal joint (DIPJ) will be

assessed as well. The ROM measurements will be recorded using Clinical Data Record Sheet as shown in Appendix J.

#### 3.6.7 Hand dynamometer and Pinch Gauge

Grip strength will be assessed with a Jamar hand dynamometer. Each participant's grip strength will be measured 3 times. Handle position 2 will be used as it is a recommended position for measuring grip strength by the American Society of Hand Therapists (Fess 1992). Meanwhile, lateral pinch strength, tripod pinch strength and tip-to-tip pinch strength will be measured by using the B&L Engineering Pinch Gauge (Mathiowetz et al. 2000). The grip and pinch strength measurements will be recorded using Clinical Data Record Sheet as shown in Appendix J.

#### 3.6.8 Purdue Pegboard Test (PPT)

The Purdue Pegboard Test (PPT) is a standardized assessment consisting of four different subtests to determine user's level of dexterity. It is composed of a board with pins, collars, and washers. In the first three subtests, the subject has to place the maximum numbers of pins into holes in the pegboard with the dominant hand, the non-dominant hand, and then with both hands simultaneously within 30 seconds. In the fourth subtest the subject uses alternate hands in order to make assemblies consisting of pins, collars, and washers, in 60 seconds. A fifth score is given by summarizing the first three sub-tests (Shahar et al. 1998). The PPT was identified as one of the top three assessments of hand dexterity for health care professionals, due to its relatively higher reliability and validity and fewer confounding variables, such as age, gender, and handedness (Lindstrom-Hazel & Veenstra 2015). The Purdue Pegboard Test results will be recorded using Clinical Data Record Sheet as shown in Appendix J.

#### 3.6.8 Box and Block Test (BBT)

The Box and Block Test (BBT) is a functional outcome measure that measures the gross manual dexterity and is commonly used across multiple clinical populations due to its benefits of ease and speed of implementation (Mathiowetz et al. 1985; Kontson et al. 2017). In the BBT, the subject is required to transfer

one hundred and fifty 2.5cm^3 wooden blocks that are placed in many different orientations on the side of the partition with the testing hand as fast as possible to another partition in one minute. A subject's score is equal to the number of these blocks transported over a 15.2-cm tall partition in one minute (Mathiowetz et al. 1985; Konston et al. 2017). The Box and Block Test had shown a high inter-rater and test-retest reliability with interclass correlations coefficients of 0.85 to 0.97 (Desrosiers et al. 1994; Platz et al. 2005; Canny et al. 2009). Mathiowetz et al. 1985 had published the normative data for the B&B Test for adults on the basis of 628 people without disabilities between ages 20 and 70+ years. The Box and Block Test results will be recorded using Clinical Data Record Sheet as shown in Appendix J.

### **3.7 ETHICAL CONSIDERATION**

Application of ethics for this research will be sent to the *Jawatankuasa Etika Penyelidikan Universiti Kebangsaan Malaysia* (JEPUKM) and the Scientific Committee of PERKESO Rehabilitation Centre. The study will commence after obtaining approval from both authority parties. Respective clinicians and staff dealing with hand injuries' patients will be informed about the study. Participation is on voluntary basis and participants have rights to withdraw from the study at any stage if they wish to do so without the exercise of any pressure or coercion. The participants will be given an information sheet about the study. Informed consent form will be given and signed by participants that agreed to participate in the study. The Information Sheet and Informed Consent Form are shown as in Appendix K. The protection of the privacy and anonymity of research participants are ensured and all information or data used for this research will only be released with consent or if required by law. The study will be registered at the Australian New Zealand Clinical Trials Registry (ANZCTR).

The ethical application for research and intervention implementation at PERKESO Rehabilitation Centre had been approved by the Scientific Committee of

PERKESO Rehabilitation Centre on the 18th November 2020 as shown with the attached Appendix L.

### **3.8 STATISTICAL ANALYSIS**

All data will be analysed using the IBM® SPSS® Statistics version 28. The study will use both descriptive and inferential statistics to analyse the data. Descriptive analysis for categorical data including gender, marital status, hand dominance, types of medical management and intervention, type of wrist fractures, educational level, employment status, and type of SOCSO compensation scheme will be expressed in frequency, percentage or/and proportion. Descriptive statistics for continuous data including age, DASH, pain, grip and pinch strength, wrist and finger ROM, hand dexterity, and work readiness scores will be expressed in mean, standard deviation, maximum, and minimum if the data is normally distributed or in median and inter-quartile range if the data is not normally distributed. The Shapiro-Wilks test will be used to test the normality of the continuous data.

The statistical analysis for each hypothesis will be tested using mixed model ANOVA by evaluating the mean differences in treatment outcomes between the groups at baseline and after 4 weeks of intervention.

Intention-to-treat (ITT) analysis will be used to analyze the difference between groups. ITT analysis, which aims to minimize bias and maintain random allocation of study participants (Gupta 2011), is suitable to be used when there are shedding participants. Its key idea is to analyse the group to which the participant belongs in that initial allocation, regardless of whether they completed the study or received the intended intervention.

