## **2.3 HYPOTHESIS**

Hypothesis 1: A 4-week combined conventional therapy and Single Joint Hybrid Assistive Limb (HAL-SJ) robotic therapy provides greater functional level improvement among workers with wrist fractures as compared to those receiving conventional therapy alone during the same intervention period as measured by the Disabilities of the Arm, Shoulder, and Hand (DASH) Outcome Measure.

Hypothesis 2: A 4-week combined conventional therapy and Single Joint Hybrid Assistive Limb (HAL-SJ) robotic therapy provides greater improvement in term of pain reduction among workers with wrist fractures as compared to those who only receive standard conventional therapy in the same intervention period as measured by the Visual Analogue Scale (VAS).

Hypothesis 3: A 4-week combined conventional therapy and Single Joint Hybrid Assistive Limb (HAL-SJ) robotic therapy provides greater improvement in term of wrist and fingers range of motion among workers with wrist fractures as compared to those who only receive standard conventional therapy in the same intervention period as measured by the goniometer.

Hypothesis 4: A 4-week combined conventional therapy and Single Joint Hybrid Assistive Limb (HAL-SJ) robotic therapy provides greater improvement in term of grip strength among workers with wrist fractures as compared to those who only receive standard conventional therapy in the same intervention period as measured by the Jamar dynamometer.

Hypothesis 5: A 4-week combined conventional therapy and Single Joint Hybrid Assistive Limb (HAL-SJ) robotic therapy provides greater improvement in term of pinch strength among workers with wrist fractures as compared to those who only receive standard conventional therapy in the same intervention period as measured by the B&L Engineering pinch gauge.

Hypothesis 6: A 4-week combined conventional therapy and Single Joint Hybrid Assistive Limb (HAL-SJ) robotic therapy provides greater improvement in term of fine dexterity of hand function among workers with wrist fractures as compared to those who only receive standard conventional therapy in the same intervention period as measured by the Purdue Pegboard Test.

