Hypothesis 7: A 4-week combined conventional therapy and Single Joint Hybrid Assistive Limb (HAL-SJ) robotic therapy provides greater improvement in term of gross dexterity of hand function among workers with wrist fractures as compared to those who only receive standard conventional therapy in the same intervention period as measured by the Box and Block Test.

Hypothesis 8: A 4-week combined conventional therapy and Single Joint Hybrid Assistive Limb (HAL-SJ) robotic therapy provides greater improvement in work readiness among workers with wrist fractures as compared to those receiving conventional therapy alone during the same intervention period as measured by the Lam Assessment of Stages of Employment Readiness (LASER).

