#### **3.3 SAMPLE SIZE**

The sample size of each hypothesis is calculated by using the G\* power analysis. Given that this is a novel study and there is no reference from previous study, sample size was calculated using ANOVA repeated measures, within-between interaction with Cohen-f effect size at 0.25 for a medium effect, alpha error at 0.05 and 80% power. Result showed that a total of 34 participants will be needed. By adding 10% dropout rate, the required sample size became 38 participants.

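### Eight hypotheses of equal standing, each sized at alpha 0.05, with no primary outcome or multiplicity rule: if any one may be cited as effectiveness, the chance of a false result favouring HAL-SJ is about 10-18%, not 2.5%

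*Combined protocol and SAP*

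**What the plan says.** Section 2.3 states eight numbered hypotheses, each that adding HAL-SJ gives more improvement than conventional therapy alone. They concern DASH, pain VAS, range of motion (ROM), grip, pinch, Purdue Pegboard, Box and Block, and LASER. Section 2.4 gathers them under one effectiveness objective with three domains: function, physical performance and work readiness. None is called primary or secondary.

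Section 3.3 treats them alike: "The sample size of each hypothesis is calculated" with "Cohen-f effect size at 0.25 for a medium effect" and "alpha error at 0.05 and 80% power", for "ANOVA repeated measures, within-between interaction". Section 3.8 adds: "The statistical analysis for each hypothesis will be tested using mixed model ANOVA". It gives no significance level, sidedness, order of testing, adjustment or success rule.

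Several hypotheses cover more than one score. Hypothesis 3 claims "greater improvement in term of wrist and fingers range of motion among workers with wrist fractures", and Appendix J has 20 active ROM lines for it. Pinch has three scores, Purdue five and Box and Block two. Section 3.6.4 scores LASER as three sub-scores, while Appendix J has one line for it. Section 3.8 does not say which score decides each hypothesis.

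**The concern.** Eight separate claims support one objective, and nothing ranks them or limits how many chances the trial has. One significant result could be reported as showing that HAL-SJ works, and the plan would not contradict it. Where a hypothesis has several scores, a second choice is open: which of them counts.

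Timing adds to this. The Gantt chart in section 3.10 starts data analysis in September 2022 and runs recruitment to June 2025, so undefined endpoints could be settled with trial data in view. A reader could not then tell a prespecified result from a selected one.

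**Working it through.** **Inputs from the plan.** Eight hypotheses (2.3); alpha 0.05, power 80%, f = 0.25, total of 34, or 38 with 10% dropout (3.3); two groups, two measurements (3.8).

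**Assumptions, not in the plan.** Each test is two-sided at 0.05, and any one significant result may be cited. Change scores, coded so that higher is better, share a common correlation r of 0 to 0.7. For the sample size, the correlation between repeated measures is 0.5, with sphericity.

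**1. The plan's own figure.** For the group-by-time interaction, lambda = N × f² × m / (1 − 0.5) = 34 × 0.0625 × 2 / 0.5 = 8.5, with 1 and 32 degrees of freedom. Power at 0.05 is 80.7%, and 34 is the smallest total that reaches 80%. With dropout, 34 / 0.9 = 37.8, so 38. Both stated figures reproduce.

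**2. Direction.** With two groups and two time points the interaction F test has 1 degree of freedom and equals a two-sided t test on change. Under no effect, half of its 5% error (2.5%) favours HAL-SJ.

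**3. Eight independent tests.**
- Either direction: 1 − 0.95^8 = 33.7%.
- Favouring HAL-SJ: 1 − 0.975^8 = 18.3%.

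**4. Correlated tests.** With c = 1.96 and k tests, the chance of at least one significant result is 1 − ∫ φ(u) [Φ((c − √r·u)/√(1−r)) − Φ((−c − √r·u)/√(1−r))]^k du. Dropping the second Φ term gives results favouring HAL-SJ only.

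| r | 8 tests, either direction | 8 tests, favouring HAL-SJ | 34 scores, either direction | 34 scores, favouring HAL-SJ |
|---|---|---|---|---|
| 0 | 33.7% | 18.3% | 82.5% | 57.7% |
| 0.3 | 30.0% | 15.2% | 69.9% | 37.3% |
| 0.5 | 25.0% | 12.5% | 53.5% | 26.9% |
| 0.7 | 19.1% | 9.5% | 35.4% | 17.7% |

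Simulated t tests on change scores with 17 per arm agree for eight tests: 33.5%, 25.3% and 19.4% in either direction at r = 0, 0.5 and 0.7, and 18.3%, 12.6% and 9.8% favouring HAL-SJ.

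Against 2.5% for one test, the eight-test rate is 9.5/2.5 = 3.8 to 18.3/2.5 = 7.3 times as high.

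**5. Count of 34 in Appendix J.** DASH 1 + LASER 1 + VAS 1 + grip 1 + pinch 3 + forearm ROM 2 + wrist ROM 4 + hand ROM 14 + Purdue 5 + Box and Block 2 = 34. Passive ROM (3.6.6) and separate LASER sub-scores would add to it.

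**6. Cost of remedies at N = 34, same assumptions.**
- One primary outcome at 0.05: power stays at 80.7%.
- Holm over seven secondary hypotheses: the first step is 0.05/7 = 0.0071, with power about 52%.
- Bonferroni over all eight: 0.05/8 = 0.00625, with power about 50%; about 55-56 participants would be needed before dropout.

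**The case against.** The strongest reply is that the plan never says one significant result is enough. The research question and general objective join function, physical performance and work readiness. If success were required in all three domains, error would not inflate in this way. If each hypothesis were reported only as itself, each would keep its own nominal error. This stands as a limit on the figures: they hold only under an any-one-counts reading, which the plan neither states nor excludes. Likewise, 0.05 appears only as a sample-size input, and the outcome correlations are assumed.

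Three stronger readings are tempting and not supported.

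- A reader might take 19-34% as the chance of falsely claiming that HAL-SJ works. That range counts differences in either direction, and one favouring control cannot support effectiveness. If every test were one-sided at 0.05, the chance of a false result favouring HAL-SJ would be about 17-34%, but the plan does not say so.
- A reader might infer that 34 tests are planned. Appendix J is a record sheet, not a list of tests. The 82.5% end also cannot apply literally, because one Purdue score is the sum of three others counted. Some Purdue and Box and Block lines would concern the uninjured hand in a one-sided fracture.
- A reader might infer that deciding scores will be picked after the data are seen. The plan is silent, so it shows only that they could be. For grip and each pinch type the sheet already provides an average of three trials.

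None of this supplies a primary outcome, a hierarchy or a rule for choosing among scores. Listing DASH first does not make it primary.

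**Conclusion.** The concern holds in a limited form. Eight hypotheses have equal standing, with no primary outcome and no multiplicity rule. If each is tested two-sided at 0.05 and any one may be cited, the chance under no effect of at least one false difference is about 19-34%. The chance of at least one favouring HAL-SJ is about 10-18%, roughly four to seven times the 2.5% of a single test. The ranges reflect assumed outcome correlations from 0.7 down to 0.

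The missing choice of deciding score for ROM, pinch, Purdue, Box and Block and LASER is a separate gap. If all 34 recorded scores were tested separately, the figures would be about 35-83% in either direction and 18-58% favouring HAL-SJ. That is a conditional illustration of what the open choice allows, not a description of the planned analysis.

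**What to change.** In section 3.8:

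- Name the DASH score at week 4 (Hypothesis 1, Specific Objective 1) as the single primary outcome, tested two-sided at 0.05. Base any overall claim of effectiveness on it alone.
- Label Hypotheses 2-8 secondary and fix one deciding score for each before any between-group results are seen. The Gantt chart makes this pressing, since it schedules analysis alongside recruitment.
- For Hypothesis 3, choose a score that covers both wrist and fingers, or reword the hypothesis. A wrist flexion-extension arc alone would not test what it states. For grip, use the three-trial average already on the record sheet.
- Either apply Holm across the seven secondary hypotheses, or report them as supportive estimates with 95% confidence intervals and no confirmatory claim. Report all other scores descriptively.

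The change is to wording, and the sample size of 34 (38 with dropout) stays. The price is paid by the secondary outcomes: they lose confirmatory standing or, under Holm, have about 52% power at the first step with 34 participants, on the assumptions that reproduce the stated sample size.

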average of 9.2 weeks of work loss following distal radius fracture (MacDermid et al. 2007). Hand injury costs had brought cumulative economy impact not only to patients, but their family, employer, and society (Dias & Garcia-Elias 2006). As the incidence of distal radius fractures rises, the short and long term costs become apparent (Nellan et al. 2012).

Stiffness and pain (Egol et al. 2014) are common complications of distal radius fractures. Loss of range of motion (ROM) is typically due to periarticular connective tissue changes after fractures, joint injuries, and immobilization (Mitchlovitz et al. 2004). Decreased wrist flexion and/or extension after trauma or surgery can be a challenging problem (McGrath et al. 2008). The ultimate goal of restoring motion is to reduce impairments and enhance functional performance for ADLs, work, and leisure.

The rehabilitation program following distal radius fractures involves three phases: immobilization phase, mobilization phase, and strengthening phase. The fundamental goals throughout these three phases include effective edema control and pain management as well as ROM, strength, and functional restorations (Mitchlovitz et al. 2001). The most frequently used therapeutic interventions following distal radius fractures include compressive wrap with retrograde massage, heat/cold modalities, joint mobilization, electrical stimulation, continuous passive motion (CPM), soft-tissue mobilization, ultrasound, splinting, ROM and strengthening exercises, and functional training (Mitchlovitz et al. 2001). The commonly used nonsurgical interventions for ROM restoration after fracture, fracture/dislocation, joint injury, or other soft tissue injuries include home exercise program and clinic based program such as splinting and casting, joint mobilization, CPM, and therapeutic exercises (Mitchlovitz et al. 2004).

Improper rehabilitation program after wrist injury may significantly impair the overall function of the upper extremity (Garcia-Elias & Folgar 2006). Both injury and patient factors can impact the management and outcomes after distal radius fracture. Although optimal strength, ROM, and function are achievable within 3-6 months of conservative or surgical management (MacDermid et al. 2007), some patients require longer duration to complete the rehabilitative phase. According to Moore and

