## **2.0 PROBLEM STATEMENT**

Most patients recovered from wrist fracture, particularly the distal radius fracture have some residual disability or pain. MacDermid et al. (2003) found that at one year following distal radius fracture, of 129 patients, there were still 46% of them experienced certain extent of difficulty with usual activities, ranging from very severe to mild. Although majority of recovery following a distal radius fracture occurred within six-months after conventional hand therapy regime, most of the patients can be expected

to still experience minimal pain and disability. Distal radius fracture cases can take up to few months and one or two years to achieve maximal functional improvement (Michlovitz et al., 2001). The residual disability or pain, along with the long functional recovery period following distal radius fracture may impact the socioeconomics of a person, family, and society significantly. With the advancement in rehabilitation technology, robotic intervention had shown positive outcomes in neurological rehabilitation programme for the past decades. However, there is a lacking of published evidence about the feasibility and effectiveness of robotic intervention in orthopaedic rehabilitation programme, especially in the field of hand therapy.

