## **INCLUSION AND EXCLUSION CRITERIA**

### **3.4.1 Inclusion criteria**

- a. SOCSO insured Malaysian workers who are on medical leave; have not returned to work; and receiving rehabilitation program at PERKESO Rehabilitation Centre.
- b. Wrist fracture involving individual or combined distal radius, distal ulna, distal radioulnar, radiocarpal joint
- c. Extraarticular fracture, partial articular fracture, and/or complete articular fracture

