### **3.4.2 Exclusion criteria**

- a. Aged below 18 years old or above 60 years old (based on SOCSO scheme)
- b. Associated peripheral nerve injuries, neuropathy or/and tendon injuries to the affected upper limb
- c. Associated neurological conditions related to the central nervous system
- d. Cognitive impairment or psychiatric condition
- e. Severe and uncontrolled medical conditions e.g. cardiovascular disorders, respiratory disorders, cancer
- f. Cardiac pacemaker
- g. Skin disorders e.g. eczema, psoriasis, open wound etc. of the affected forearm and hand that prevent electrode placements
- h. Severe contracture of the affected wrist joint
- i. Forearm size that is not fit to wear the Single Joint Hybrid Assistive Limb (HAL-SJ) robotic exoskeleton

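### Time since fracture is unrestricted and its date collected, yet the analysis ignores it; adding it and the baseline score as covariates is a free improvement

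*Combined protocol and SAP*

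**What the plan says.** Analysis. Section 3.8 tests every hypothesis with a "mixed model ANOVA by evaluating the mean differences in treatment outcomes between the groups at baseline and after 4 weeks of intervention". It names no covariate, stratum or subgroup. The continuous variables it lists for description are age and the outcome measures; time since injury is not among them.

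Eligibility. Section 3.4.1 admits "SOCSO insured Malaysian workers who are on medical leave; have not returned to work; and receiving rehabilitation program at PERKESO Rehabilitation Centre", subject to fracture site and type. None of the nine exclusions in 3.4.2 is expressed in time since injury. The nearest to a limit on chronicity is "Severe contracture of the affected wrist joint".

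Recovery. Section 2.0 says that the "majority of recovery following a distal radius fracture occurred within six-months after conventional hand therapy regime", and then: "Distal radius fracture cases can take up to few months and one or two years to achieve maximal functional improvement". The Introduction adds that "optimal strength, ROM, and function are achievable within 3-6 months of conservative or surgical management".

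Data. The questionnaire in 3.6.2 records the "history of present injury including date of injury, mechanism of injury, medical/surgical" management and the date of surgery, and Appendix B has fields for both dates.

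Allocation and size. Section 3.5 (items f and g) describes simple, concealed randomisation with equal numbers of cards for the two groups and no stratification. Section 3.3 gives 34 participants, raised to 38 for 10% dropout.

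**The concern.** It follows from the protocol's account of recovery that a worker's improvement over any four weeks depends partly on how long ago the fracture was. Workers early in healing and workers close to their plateau can enter the same comparison, and nothing in allocation or analysis takes account of it.

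Two things follow in a trial of this size. The spread in natural recovery stays in the error term, which costs precision. And if the arms happen to differ in time since injury, the estimated effect moves with that difference. Because 3.8 does not plan to describe the variable, such a difference could also pass unreported.

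Having baseline as one of the two time points does not settle this. With two time points the group-by-time test is a test of change, and time since injury bears on the rate of change. Nor does the starting score fully stand in for it: the same DASH score may belong to a worker still healing or to one left with residual disability.

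**Working it through.** **1. The plan's own figure.** Inputs from 3.3: f = 0.25, alpha 0.05, power 80%, within-between interaction. Groups k = 2 and time points m = 2 follow from the design. The correlation between repeated measures, rho, is not stated; I assume 0.5. With lambda = f² × N × m/(1 − rho), N = 34 gives 0.0625 × 34 × 2/0.5 = 8.5 on (1, 32) degrees of freedom, and power 0.807. So 34 reproduces, and 34/0.9 = 37.8 rounds up to 38. (rho = 0.3 would need 46 and rho = 0.7 would need 22.) In SDs of change the planned effect d satisfies lambda = N × d²/4, so d = sqrt(4 × 8.5/34) = 1.0.

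**2. Chance imbalance.** With 19 per arm the standardised difference in mean time since injury has SD sqrt(2/19) = 0.324.
- P(difference > 0.25 SD, either way) = 2 × P(Z > 0.25/0.324) = 44%
- P(difference > 0.5 SD, either way) = 2 × P(Z > 0.5/0.324) = 12%

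**3. What an imbalance does.** The unadjusted estimate shifts by r × imbalance, in SDs of change, where r is the size of the correlation between time since injury and 4-week change. The documents give no r, so it is an assumption. At an imbalance of 0.5 SD:

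| r | Shift (SD of change) |
|---|---|
| 0.1 | 0.05 |
| 0.3 | 0.15 |
| 0.5 | 0.25 |

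These compare with a planned effect of 1.0 SD. In simulated trials of 38 with exactly that imbalance, the unadjusted test rejects a true null in 6% (r = 0.3) or 8% (r = 0.5) of trials, against about 5% after adjustment. If the imbalance goes against the robot arm, power is 73% or 63% unadjusted and 86% or 92% adjusted.

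**4. How large r and the gain might be.** Assume exponential recovery with a fraction c complete at 180 days, so tau = −180/ln(1 − c). The ratio of expected 4-week recovery for entry at day 42 to that for entry at day 180 is exp(138/tau):

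| c at six months | tau (days) | Ratio |
|---|---|---|
| 50% | 259.7 | 1.7 |
| 75% | 129.8 | 2.9 |
| 90% | 78.2 | 5.8 |

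Section 2.0 says only that most recovery falls within six months, which allows anything from the first row (its lower limit) to the last. I then simulated DASH under assumed values: time since injury lognormal with median 90 days and log-SD 0.6 to 0.8, cut at 21 and 540 days; initial deficit 50 (SD 12); plateau 25 (SD 10 to 20); measurement error SD 3 to 5. Across the three curves, change correlates about 0.1 to 0.57 with log time since injury. Adding person-to-person variation in response lowers this to 0.04 to 0.32. Beyond adjustment for the baseline score, log time removes 0 to 23% of residual variance, mostly under 3%. The top of that range needs the steepest curve and little noise.

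**5. Gain and cost in power.** At N = 34, analysing change with time since injury as the only covariate, lambda becomes 8.5/(1 − r²) on (1, 31) degrees of freedom. Power is 0.841 at r = 0.3 and 0.903 at r = 0.5. At r = 0 it is 0.806 against 0.807. Spending a second degree of freedom with no return, lambda 8.5 on (1, 30), gives 0.805.

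**The case against.** The strongest reply is that the trial is randomised with concealed allocation, both arms heal, and both receive the same conventional therapy. The unadjusted contrast is therefore unbiased on average and its overall type I error holds. That stands in full. With the limits of what the documents state, it rules out several stronger readings that a reader might infer:

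- *The estimate is biased.* It is not. A shift arises only given an imbalance that happened by chance, and an imbalance above 0.5 SD has a 12% probability, so large differences should not be called frequent.
- *Natural healing is the main rival explanation for the result.* It would be in a single-arm study. Here the control arm accounts for it, apart from chance imbalance.
- *Natural recovery differs several-fold between entrants.* The ratio of 5.8 needs 90% recovery at six months. The documents give no such fraction, and at 50% the ratio is 1.7.
- *All eight hypotheses would move the same way.* Only DASH was modelled, and nothing in the documents ties work readiness on the LASER to time since fracture in that manner.
- *Workers enter at literally any time.* Medical leave, not being back at work, current rehabilitation and the contracture exclusion narrow the range indirectly, though none sets a limit.

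It is also fair to say that the gain beyond the baseline score may be close to nil, and that the descriptive list in 3.8 is not worded as exhaustive. Neither point argues against naming a variable the trial already holds.

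**Conclusion.** The point holds as a matter of precision and protection against chance imbalance, not validity. The documents establish that there is no time window, that recovery depends on time, that the date is collected, that allocation is unstratified, and that no covariate is planned. The imbalance probabilities rest only on 19 per arm and a normal approximation. The size of the consequence rests on r, which the documents do not give: a shift of 0.05 to 0.25 SD of change for r from 0.1 to 0.5 at a 0.5 SD imbalance. The gain over baseline adjustment alone is probably small. The recommendation does not depend on it being large, because the loss if r = 0 is negligible. This is a free improvement; the trial is not unsound without it.

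**What to change.** In 3.8, replace the group-by-time test with an ANCOVA, pre-specified for each hypothesis: the week-4 value of the outcome on allocated group, the baseline value of that outcome, and log(days from date of injury to baseline assessment). Add time since injury to the variables described, and report it by arm in the baseline table.

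The cost is wording in 3.8 and at most two degrees of freedom. No new data, visits or change of sample size are needed. The Gantt chart in 3.10 runs data analysis alongside recruitment from 2022, so the change should be dated and made before outcomes are compared by arm; added afterwards, it would look data-driven.
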